## Abstract

**Background:**

The Oxford–Royal College of General Practitioners (RCGP) Research and Surveillance Centre (RSC) and Public Health England (PHE) are commencing their 54th season of collaboration at a time when SARS-CoV-2 infections are likely to be cocirculating with the usual winter infections.

**Objective:**

The aim of this study is to conduct surveillance of influenza and other monitored respiratory conditions and to report on vaccine uptake and effectiveness using nationally representative surveillance data extracted from primary care computerized medical records systems. We also aim to have general practices collect virology and serology specimens and to participate in trials and other interventional research.

**Methods:**

The RCGP RSC network comprises over 1700 general practices in England and Wales. We will extract pseudonymized data twice weekly and are migrating to a system of daily extracts. First, we will collect pseudonymized, routine, coded clinical data for the surveillance of monitored and unexpected conditions; data on vaccine exposure and adverse events of interest; and data on approved research study outcomes. Second, we will provide dashboards to give general practices feedback about levels of care and data quality, as compared to other network practices. We will focus on collecting data on influenza-like illness, upper and lower respiratory tract infections, and suspected COVID-19. Third, approximately 300 practices will participate in the 2020-2021 virology and serology surveillance; this will include responsive surveillance and long-term follow-up of previous SARS-CoV-2 infections. Fourth, member practices will be able to recruit volunteer patients to trials, including early interventions to improve COVID-19 outcomes and point-of-care testing. Lastly, the legal basis for our surveillance with PHE is Regulation 3 of the Health Service (Control of Patient Information) Regulations 2002; other studies require appropriate ethical approval.

**Results:**

The RCGP RSC network has tripled in size; there were previously 100 virology practices and 500 practices overall in the network and we now have 322 and 1724, respectively. The Oxford–RCGP Clinical Informatics Digital Hub (ORCHID) secure networks enable the daily analysis of the extended network; currently, 1076 practices are uploaded. We are implementing a central swab distribution system for patients self-swabbing at home in addition to in-practice sampling. We have converted all our primary care coding to Systematized Nomenclature of Medicine Clinical Terms (SNOMED CT) coding. Throughout spring and summer 2020, the network has continued to collect specimens in preparation for the winter or for any second wave of COVID-19 cases. We have collected 5404 swabs and detected 623 cases of COVID-19 through extended virological sampling, and 19,341 samples have been collected for serology. This shows our preparedness for the winter season.

**Conclusions:**

The COVID-19 pandemic has been associated with a groundswell of general practices joining our network. It has also created a permissive environment in which we have developed the capacity and capability of the national primary care surveillance systems and our unique public health institute, the RCGP and University of Oxford collaboration.

## Introduction

### Background

The Oxford–Royal College of General Practitioners (RCGP) Research and Surveillance Centre (RSC) is a network of general practices and is now in its 54th season of surveillance and vaccine effectiveness in its long-standing collaboration with Public Health England (PHE) and predecessor bodies [1]. This season is complicated by the likely cocirculation of SARS-CoV-2 and its associated disease burden [2].

The RCGP RSC has been recruited as a nationally representative population [3] that provides pseudonymized data for surveillance of infectious diseases. However, the recent influx of practices may mean we have to adjust for practice distribution and ensure we recruit virology sampling practices that are evenly distributed. The disease surveillance program is commissioned by PHE and monitors 38 infectious diseases, including influenza; at the start of 2020, monitoring extended to include COVID-19 [4].

The recently expanded RCGP RSC extracts pseudonymized data from over 1700 general practices each week covering a nationally representative [3] population of over 13 million. Data from these practices are reported online in the RCGP’s Weekly Return [5], which includes monitoring weekly rates of influenza-like illness (ILI) and other communicable and respiratory diseases for England. We also produce an annual report [6]. The RCGP RSC data set includes all coded data and all prescribed items, including vaccine exposure [3]. To manage our extended network of practices, we have set up a new analytics hub: the Oxford–Royal College of General Practitioners Clinical Informatics Digital Hub (ORCHID) [7].

The RCGP RSC conducts virology surveillance each influenza season. Given the onset of COVID-19, virological sampling has expanded to approximately 300 general practices (see Figure 1). We have reported on which groups of patients were more likely to test positive for COVID-19 [8], on excess mortality [9], and the shift away from face-to-face consultations during the first wave of COVID-19 pandemic [10].

The RCGP RSC is also active in serosurveillance. During the 2018-2019 influenza season, we successfully conducted our first collection of serological samples from adults, linking them to their respective medical records [11,12]. Sentinel networks can provide a mechanism for systematic data collection and linkage to medical records and health outcomes [13], as well as sampling across the complete age range [14]. Current activity has included supporting PHE household studies and collecting convalescent sera from people previously infected with COVID-19.

Finally, the RCGP RSC network has supported trials and studies designated as high-priority public health research. These included recruiting to the PRINCIPLE (Platform Randomised trial of INterventions against COVID-19 In older peoPLE) trial [15] and supporting recruitment to RAPTOR-C19 (RAPid community Testing fOR COVID-19) [16].

This protocol sets out how the RCGP RSC will continue to provide enhanced passive surveillance, virological and serological surveillance from a subset of practices, and support high-priority public health research.

**Figure 1 figure1:**
[figure not shown]
Royal College of General Practitioners Research and Surveillance Centre’s virology sampling sites in England. Distribution by type of computerized medical record system is shown. EMIS: Egton Medical Information Systems; INPS: In Practice Systems; TPP: The Phoenix Partnership.

### Aim

The aim of this protocol is to provide comprehensive surveillance of influenza, COVID-19, and other monitored conditions including health outcomes. The RCGP RSC network will also collect samples for virological and serological analysis, measure vaccine exposure and effectiveness, and support other high-priority public health research.

### Objectives

Our six objectives are as follows:

To conduct surveillance of influenza and other monitored respiratory conditions, including COVID-19. This will be primarily from primary care data but will also include linkage to secondary care and mortality data sets to enable reporting of health outcomes. We will provide observatories, dashboards, and training to optimize data quality.To collect virological and serological samples to report the presence and spread of monitored conditions from a nationally representative sample of practices.To report vaccine uptake, estimate effectiveness, and investigate adverse events of interest (AEIs). We will focus on influenza vaccinations and possible new COVID-19 vaccines.To support research to answer important public health questions, including trials of early interventions in the community, near-patient testing, and household spread.Apply the Findable, Accessible, Interoperable, and Reusable (FAIR) principles so that our data are findable, accessible, interoperable, and reusable by other organizations.To implement appropriate information and research governance.

## Methods

### Overview

The methods include six components: (1) surveillance of influenza, COVID-19, other monitored conditions, and associated health outcomes; (2) virological surveillance and serosurveillance; (3) monitoring vaccine uptake and effectiveness; (4) supporting priority public health research; (5) data curation; and (6) governance.

### Surveillance of Influenza, COVID-19, Other Monitored Conditions, and Associated Health Outcomes

We will collect pseudonymized, routinely collected, coded clinical data, which has been coded into patient records, using UK Systematized Nomenclature of Medicine Clinical Terms (SNOMED CT) codes (SNOMED International), for enhanced passive surveillance. This will entail a wide range of clinical event data, including collection of monitored conditions, vaccine exposure, AEIs, hospital admissions, intensive care, and deaths, to monitor approved study outcomes and for any unexpected public health emergencies. Effective interoperability and communication will be facilitated by monthly pseudonymized linkage, facilitated by NHS (National Health Service) Digital and PHE [7], to secondary care and other data sources, including Secondary Uses Service, the continuously updated source of hospital data (see Textbox 1).

Linkage to other data sets to support surveillance and research; individual data sets may have limitations on their use to specific projects and users.
**NHS (National Health Service) Digital:**
Cancer Registration Data (reduced)Secondary Uses Service (SUS) Payment by Results EpisodesSUS Payment by Results OutpatientsSUS Payment by Results Accident and EmergencySUS Payment by Results SpellsMental Health Services Data SetDiagnostic Imaging DatasetEmergency Care Data Set (ECDS)COVID-19 Hospitalisation in England Surveillance System (CHESS) Dataset-CV19 NHS 111 OnlineSecond Generation Surveillance System (SGSS): laboratory test reportsHospital Episode Statistics (HES; same granularity of supply as for SUS)Office of National Statistics (ONS) MortalityNHS 111 (free-to-call single nonemergency number medical helpline)
**National Cancer Registration and Analysis Service (NCRAS):**
Cancer Registry (full)Chemotherapy data setRadiotherapy data set

We have converted all our primary care coding to SNOMED CT coding and are using this throughout our data processing [17] (see Multimedia Appendix 1). We have been at the forefront of ensuring that primary care systems code cases correctly and that we comprehensively capture historic data [18]. This has included the development of database-linked tools to programmatically search SNOMED CT for relevant tools. The hierarchical nature of SNOMED CT is that it requires machine searching rather than manual searching (see Multimedia Appendix 2). This will continue to deliver effective COVID-19 surveillance in parallel with the annual influenza surveillance this season.

We will enhance surveillance through the provision of dashboards and observatories to provide feedback about levels of care compared to other practices in our network and to improve data quality, clinical care, and patient safety. There will be a particular focus on data quality, including the recording of ILIs, the use of the RCGP RSC case definition (see Textbox 2 [19-21]), recording of upper and lower respiratory tract infections, and recording of suspected COVID-19 cases, with an emphasis on recording episode type (ie, whether this is a new case or a follow-up). We will programmatically adjust for when episode type is not recorded [18,22].

This year we will extend our virology sampling window to 10 days. We will also report on health outcomes, including mortality [9] (see Figure 2).

Royal College of General Practitioners (RCGP) Research and Surveillance Centre (RSC) case definitions of influenza-like illness (ILI).
**The RCGP RSC definition of ILI:**
An acute respiratory illness with a temperature measured as, reported as, or plausibly ≥38 °C and cough, with onset within the past 10 days.  ILI cases should not have another more plausible diagnosis. ILI cases have a sudden onset, and there are often symptoms suggestive of systemic upset—myalgia, fatigue, malaise, headache, etc.  RCGP RSC stresses the notion of symptoms within 10 days of onset to differentiate acute episodes, with swabs only wanted within 7 days of onset.This definition is compatible with the World Health Organization (WHO) and European Centre for Disease Prevention and Control (ECDC) definitions [19,20]. The WHO definition has the highest specificity (21.4%) and the ECDC definition has the highest sensitivity (96.1%) [21].

**Figure 2 figure2:**
[figure not shown]
Royal College of General Practitioners Research and Surveillance Centre observatory showing mortality through the first wave of the COVID-19 pandemic in England. Deaths per 100,000 population are displayed over the International Organization for Standardization (ISO) weeks for 2019 and 2020.

### Virological Surveillance and Serosurveillance

A volunteer subset of practices will conduct virological surveillance (see Multimedia Appendix 3). They will conduct or arrange virological sampling of patients presenting with ILI or lower respiratory tract infection, including acute bronchitis and bronchiolitis in children under the age of 5 years. We will include those suspected to have, or have been exposed to, COVID-19 who have persistent cough, loss of taste and/or smell, shortness of breath, history of fever, and/or the presence of a wheeze. We will look for practices to collect 20 samples per week; additional samples can be collected if the spread that is present is within a household or a communal establishment. Practices will receive feedback via dashboards [23] (see Textbox 3 [5,24-28]). Our target is to collect 600 samples per week across all age bands.

The anticipated changes in the coming year are as follows:

We will reduce the burden of information collected on the virology request form. Thus, a common but reduced set of data will be collected for all patients offered virology sampling. Vaccination history and a record of their comorbidities will have already been collected electronically as part of the standard data extract. However, we will stress the importance of recording the NHS number as a unique identifier, to help ensure efficient linkage of clinical data to test results.People who volunteer to self-swab will be given a voucher code they can use online to arrange for a sample to be sent; those in the surgery will have a swab taken by their general practitioner or practice team, and this will be sent through the post to the PHE reference laboratory. Patients taking self-swabs should be given their NHS number to include in their swab request to improve data matching.All results will be sent to practices online via the e-Lab system [29]; patients who self-swab and provide a mobile number will additionally receive their results by text message (see Figure 3).

Dashboards, online support, and observatories—also called weekly returns—to monitor and support data recording and key public health projects.
*Practice Dashboard*
My Practice Dashboard [24]
**All practices:**
Seasonal wellness: all practices can see vaccine uptake and incidence of key monitored conditionsCOVID-19: all practices will compare their incidence of COVID-19 with the rest of the network
**Volunteer practices involved in specific surveillance or trials:**
Virology: for practices participating in specimen collection; in-practice and home testsSerology: for practices to observe their serology sampling; primarily by age bandPRINCIPLE (Platform Randomised trial of INterventions against COVID-19 In older peoPLE ) trial: to help practices know their level of recruitmentOnline support:Facebook page [25]Twitter account [26]Podcast [27]
*Observatories and Weekly Returns*

**Oxford–Royal College of General Practitioners (RCGP) Research and Surveillance Centre (RSC) weekly return:**
Twice weekly report—during the pandemic—on influenza, COVID-19, and other monitored conditions; reports are published at the RCGP RSC website [5]—follow the “RSC Communicable and Respiratory Disease report” link on the “Public Health Data” page; this is the 54th year of this report
**Observatories [28]. We produce weekly reports online for the observatories, which provide an interactive weekly return of national data; these are as follows:**
Seasonal wellnessCOVID-19MortalityVirology samplingSerology samplingPRINCIPLE trial eligible patients

**Figure 3 figure3:**
[figure not shown]
Flowchart for case identification and sampling for the 2020-2021 season surveillance. The National Health Service (NHS) number is a vital unique identifier for all forms across virology and serology, including for patients requesting a test kit at home. ILI: influenza-like illness; LRTI: lower respiratory tract infection; PHE: Public Health England; PRINCIPLE: Platform Randomised trial of INterventions against COVID-19 In older peoPLE; SoB: shortness of breath.

A volunteer group of practices will also participate in serological surveillance. The largest project will be the opportunistic collection of an extra blood sample from patients undergoing a routine blood test. Practices will be asked to collect across age bands (aged 10 years and above) (see Figure 4), with feedback provided to general practices via a dashboard and overall via an observatory [30]. We are now recruiting practices from areas with more ethnically mixed populations to provide greater insight into disease spread in ethnic minority populations. Other serology projects include extended serosurveillance in a subset of patients with positive virology tests (n=63) as well as recruiting and sampling patients included in the PHE-led household contacts of confirmed COVID-19 cases (HOCO) study [30]. We are piloting responsive surveillance in areas with higher disease incidence.

**Figure 4 figure4:**
[figure not shown]
Number of serological surveillance samples collected per week. The program was initiated in week 11; we have been taking active steps to encourage similar numbers across age bands per week.

### Monitoring Vaccine Uptake, Effectiveness, and Adverse Events of Interest

Capturing vaccine exposure is critical to conducting vaccine effectiveness studies. With an increasing range of vaccines available, capturing exposure data when not recorded within the practice, beyond the fact that a vaccine has been given, presents significant challenges [31]. Further issues include difficulties capturing vaccine batch numbers [32]. We will ask practices to preload the vaccine brands and batch numbers online.

We plan to continue to report AEIs following vaccination using routinely collected data, though we would have the capability to provide patient AEI reporting cards if commissioned for COVID-19 or other vaccines [33,34]. Practices will be provided with prompts to improve coding. Good data quality regarding AEI recording may identify any differences between influenza vaccine types, to elucidate whether egg- or cell-based vaccines with or without adjuvants are associated with different rates of AEIs. There may also be up to six types of COVID-19 vaccines available for which we may be able to provide uptake and AEI data.

### Supporting Priority Public Health Research

#### Overview

The RCGP RSC will support a range of research (see Multimedia Appendix 4), with the PRINCIPLE [15] and RAPTOR-C19 [16] trials as the top priorities. The RCGP RSC is a member of a number of European studies, including a point-of-care testing study and data sharing as part of the DRIVE (Development of Robust and Innovative Vaccine Effectiveness) consortium [35,36] and a European study of respiratory syncytial virus epidemiology [37]. In partnership with PHE, we are also members of the I-MOVE (Influenza–Monitoring Vaccine Effectiveness in Europe) consortium, which has extended its work into COVID-19 [38].

We will support two ethically approved generic protocols for COVID-19 research: DECISION-COVID (DEfining the CharacterIStIcs Of Individuals with suspected Novel COronaVIrus Disease and risk factors for development of the disease) and MAINROUTE (Monitoring Attendance, INvestigation, Referral, and OUTcomEs in primary care: impact of and recovery from COVID-19 lockdown). DECISION-COVID provides a framework for looking at medications that might impact on COVID-19 outcomes; MAINROUTE assesses the impact of lockdown on the wider implications to care (see Multimedia Appendix 4). We have already reported on how lockdown has led to a reorganization of primary care service delivery [10]; in addition, we are part of the RECAP (Remote COVID-19 Assessment in Primary Care) early warning score validation study, which was set to start in September 2020 [39].

#### Statistical Methods

A range of statistical methods will be used that are appropriate to the area of surveillance or the research undertaken. We will use propensity matching and a wide range of other methods to work within the constraints of routine data [40].

Vaccine effectiveness will be assessed using test-negative design [41,42]. Patients meeting the predefined clinical criteria will undergo laboratory testing for specific circulating viruses. Patients who test positive will comprise the cases; patients who test negative to both influenza and COVID-19 will form the control group. In the clinical at-risk populations, as defined by NHS England, vaccine effectiveness will be calculated as follows: (1 − adjusted vaccination odds ratio) × 100% [42]. This will be estimated overall and stratified by influenza virus subtype for all ages. Cohort analysis will also be performed with vaccine effectiveness estimated as 1 – risk in vaccinated subjects and 1 – risk in unvaccinated subjects, with adjustment for confounding variables.

We will report AEIs using self-controlled case series design [43,44]. An exposure period will be identified shortly after vaccination, and a baseline period will form the remainder of the observation period. The frequency of AEIs will be compared to identify any invariant confounding [44,45]. We will use self-controlled case series to report the different rates of AEIs between vaccines; biases should be similar between vaccines. For influenza, we will continue to use the European Medicines Agency–specified AEIs; should COVID-19 vaccination commence this season, we will identify AEIs. Notwithstanding the enlarged size of the network, we are not large enough to detect rare events.

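### The cohort vaccine-effectiveness formula gives two event-free proportions and no contrast between vaccinated and unvaccinated, so it is wrong as written

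*Protocol article*

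**What the plan says.** The Statistical Methods section gives two routes to vaccine effectiveness. The first is the test-negative design, for which "vaccine effectiveness will be calculated as follows: (1 − adjusted vaccination odds ratio) × 100" per cent. The second follows in the same paragraph: "Cohort analysis will also be performed", with "vaccine effectiveness estimated as 1 – risk in vaccinated subjects and 1 – risk in unvaccinated subjects", and "with adjustment for confounding variables".

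Estimating effectiveness is part of the third of six objectives in the Objectives section. No other section restates or corrects the cohort formula, and the article gives no attack rate in vaccinated or unvaccinated patients.

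**The concern.** A VE measure has to compare the two groups and has to be 0% when vaccination makes no difference. The test-negative formula does both, because an odds ratio of 1 gives 0%. The cohort formula does neither. It names the risk in each group but joins the two with a conjunction where a division is needed, so the reader is left with two complements of risk.

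Taken literally, the cohort analysis would report numbers governed mainly by how common the infection was that season. They would be close to 100% whenever the risk is low, whatever the vaccine did. They could not be set beside the test-negative results. The Conclusions section also offers the approach to other surveillance groups for their own use, so a wrong formula could be copied.

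**Working it through.** The article states no cohort VE, attack rate or sample size, so there is no published figure to reproduce. The check is algebra over assumed risks.

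**Inputs (all assumed).** Risk in the unvaccinated, ru: 0.5%, 1%, 2%, 5%, 10%, 20%. True VE: 0% and 60%. Risk in the vaccinated: rv = ru × (1 − VE).

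**Formulas.** As written: 1 − rv and 1 − ru. Standard: 1 − rv/ru.

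| ru | True VE | rv | 1 − rv | 1 − ru | 1 − rv/ru |
|---|---|---|---|---|---|
| 0.5% | 0% | 0.5% | 99.5% | 99.5% | 0% |
| 0.5% | 60% | 0.2% | 99.8% | 99.5% | 60% |
| 1% | 0% | 1% | 99.0% | 99.0% | 0% |
| 1% | 60% | 0.4% | 99.6% | 99.0% | 60% |
| 2% | 0% | 2% | 98.0% | 98.0% | 0% |
| 2% | 60% | 0.8% | 99.2% | 98.0% | 60% |
| 5% | 0% | 5% | 95.0% | 95.0% | 0% |
| 5% | 60% | 2% | 98.0% | 95.0% | 60% |
| 10% | 0% | 10% | 90.0% | 90.0% | 0% |
| 10% | 60% | 4% | 96.0% | 90.0% | 60% |
| 20% | 0% | 20% | 80.0% | 80.0% | 0% |
| 20% | 60% | 8% | 92.0% | 80.0% | 60% |

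Two things follow. With an ineffective vaccine, each term as written is 1 − ru, so it runs from 80% to 99.5% over this range and is never 0%. At ru = 2%, moving from a useless vaccine to one that is 60% effective shifts the vaccinated term only from 98.0% to 99.2% and leaves the other term where it was.

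**Can the two terms be combined into a VE?** Take ru = 2% and true VE = 60%.

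- Ratio: 0.992 / 0.980 = 1.012, and 1 − 1.012 = −1.2%.
- Difference: 0.992 − 0.980 = 1.2 percentage points, which is the absolute risk reduction ru − rv.

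Both combinations are zero for a useless vaccine, but neither returns 60%.

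**Does adjustment rescue it?** No. Adjusting each term for confounders gives two adjusted event-free proportions. The sentence names no adjusted risk, rate, odds or hazard ratio.

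**The case against.** The best defence is that this is plainly a slip. The correct form of a relative measure stands earlier in the same paragraph, both risks are named, and an experienced analyst would compute 1 minus the risk ratio without being told. The cohort analysis is also an addition to the test-negative analysis, whose formula is sound. All of that stands, and it limits the consequence. It does not make the sentence right. An article may leave detail to a fuller document, but here it states an estimator, and states it wrongly.

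Three stronger readings are tempting, and the document does not support them.

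- **That the formula returns about 98% for a useless vaccine.** That figure is only 1 minus an assumed 2% risk. The article supplies no risk, and the formula yields two values.
- **That a primary objective is compromised.** The six objectives are not ranked, and effectiveness is one part of one of them.
- **That vaccination status is fixed at the end of the season, so time before vaccination is credited to the vaccinated (immortal-time bias).** The text speaks of vaccinated and unvaccinated subjects and is silent on how status is assigned over time. A condensed article may leave that to the full plan, so no bias of this kind can be claimed.

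**Conclusion.** Wrong as written. The cohort expression does not define vaccine effectiveness: it forms no contrast, it has no null value of 0%, and its scale does not match the test-negative estimator beside it. For a vaccine with no effect it gives two equal values between 80% and 99.5% for assumed risks of 20% down to 0.5%. That range rests on the assumed risks. The absence of a contrast does not depend on any of them.

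The scope is narrow. The cohort analysis is affected and the test-negative analysis is not. The intended quantity was very probably 1 minus the risk ratio.

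**What to change.** Replace the cohort expression with:

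VE = (1 − adjusted risk in vaccinated / adjusted risk in unvaccinated) × 100%

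This is 1 minus the adjusted relative risk. In the table above it returns 0% for a useless vaccine and 60% when 60% is true, at every assumed risk. It also has the same null value as the test-negative formula.

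The cost is one sentence of wording. The correction needs no new data and no change of design.
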